#### Clinical evaluation

Independent *t*-tests and *χ*2-tests will be used to estimate between-group differences in demographics and pre-treatment measures at baseline. Outcomes on continuous outcome variables at T1, T2 and T3 will be analysed via mixed-model analyses, with participants as random effects, and time (T1-T3), group (bCBT vs. TAU) and time x group as fixed effects, with baseline scores as a single covariate. To assess the magnitude of treatment effects, Cohen’s *d* effect sizes [72] for each time point will be calculated by dividing MM parameter estimates of fixed effects at each post-treatment assessment by the pooled standard deviation of baseline scores. Effect sizes under 0.2 are deemed to be small, 0.5 to be moderate and 0.8 to be large [72].

Differences in response and remission rates, as well as adherence rates will be examined using *t*-tests and *χ*2-tests. In addition, moderator analysis will be conducted for demographic variables such as gender, age, educational level, partner status, employment status, as well as treatment and patient characteristics.

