### Assessments

Measures will be taken at baseline and at 3, 6 and 12 months after baseline. The diagnostic interview (M.I.N.I.) at baseline will be conducted by telephone by trained interviewers. At 12 months follow-up the depression, anxiety and PTSD sections of the M.I.N.I. will be assessed again by telephone by an interviewer blinded to treatment allocation. All other assessments will be performed online via a link to the self-report questionnaires sent by e-mail. Table 2 provides an overview of the measures and their time of assessment.

**Table 2 Tab2:** Overview of measures

Variable	Instrument	T0^*^	T1^*^	T2^*^	T3^*^
*Measures taken from patient*					
Demographics (patient characteristics)		X			
Current and history of treatment		X			
Diagnosis of depression and comorbid disorders	M.I.N.I. 5.0	X			X
Depressive symptoms	PHQ-9	X	X	X	X
Depressive symptoms & severity	QIDS-SR-16	X	X	X	X
Health related well-being (QALY)	EQ-5D-5L	X	X	X	X
Health care uptake and productivity losses TIC-P	TIC-P	X	X	X	X
Sense of mastery	SOMS	X	X	X	X
Treatment preference		X			
Patient expectancy	CEQ	X			
Therapeutic alliance	WAI-SF-PT		X		
Technology alliance	WAI-Online Therapy^a^		X		
Client satisfaction with treatment	CSQ-8		X		
Satisfaction with the online program SUS	SUS^a^		X		
Possible negative side-effects	INEP			X	
*Measures taken from therapist*					
Therapeutic alliance	WAI-SF-TH^b^		X		
Satisfaction with the online program	SUS^c^		X		

^a^Offered to condition receiving blended treatment only

^b^Has to be completed for each patient. Offered at the same time point as T1 assessment of the patient

^c^Has to be completed once per therapist after completion of the first blended treatment

*T0 refers to baseline and T1, T2 and T3 to the 3, 6 and 12 month questionnaires

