### Sample size

For the European study as a whole, the sample size calculation is based on the non-inferiority design and calculated for the primary clinical outcome symptoms of depression. The non-inferiority margin was set at ∆Cohen’s d = 0.20, which is a conservative estimate of the subjective minimal important difference that is noticeable by patients [66]. To determine that there is no difference between blended depression treatment and TAU on the primary clinical outcome, a total of 1052 patients is required to be 90 % certain (power of .90) that the lower limit of the two sided 95 % confidence interval will be above the non-inferiority limit of Cohen’s *d* = -0.2. To allow for expected drop-out and variation between settings, the total number of participants to be recruited will be 1200.

For the current trial in the Netherlands we aim to include 156 participants (78 per arm). This sample size will be sufficient to be 80 % sure (i.e. power = 1-ß = 0.80) that the lower limit of a one-sided 95 % confidence interval (or equivalently a 90 % two-sided confidence interval) will be above a non-inferiority limit of -0.4 if we assume that there is no difference between the standard and blended depression treatment. A margin of 0.4 was judged acceptable, as this range of small to moderate difference in effect size will not result in clinically important differences [67].

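### The participant random effect in the clinical model implies one variance for 3, 6 and 12 months, so an interval at a single visit is miscalibrated if that variance changes over follow-up

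*Protocol article*

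**What the plan says.** Clinical evaluation (under Planned statistical analyses) fits a mixed model to the scores at T1, T2 and T3 "with participants as random effects, and time (T1-T3), group (bCBT vs. TAU) and time x group as fixed effects" and "with baseline scores as a single covariate". It names no random slope and no residual covariance structure. Cohen's d for each time point is obtained "by dividing MM parameter estimates of fixed effects at each post-treatment assessment" by the pooled baseline SD.

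The Assessments section sets the visits: "Measures will be taken at baseline and at 3, 6 and 12 months after baseline". Blended intervention gives a treatment course of 19-20 weeks, so the first follow-up falls during treatment, the second after it and the third well after it.

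The Sample size section states the non-inferiority criterion for the Dutch trial. It concerns "the lower limit of a one-sided 95 % confidence interval (or equivalently a 90 % two-sided confidence interval"), which "will be above a non-inferiority limit of -0.4 if we assume that there is no difference". It names no visit for this test.

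**The concern.** A participant random effect with independent residuals allows two covariance parameters: a between-participant variance and a residual variance. This makes the total variance the same at every visit and the covariance the same for every pair of visits. Yet the plan reads a separate treatment effect at each visit, and under this model the standard error of each comes from a pooled variance, not from that visit's own.

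The three visits sit at different stages of treatment and follow-up, so equal variance is a real restriction. Patients may spread out as some recover and others do not. The relation to baseline may also fade with time. Either would raise the baseline-adjusted variance at the later visit. In a non-inferiority trial, an interval that is too narrow makes it easier to declare non-inferiority wrongly.

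**Working it through.** **Inputs from the Sample size section.** "we aim to include 156 participants (78 per arm"); margin 0.4 SD; one-sided 5%; "This sample size will be sufficient to be 80 % sure (i.e. power = 1-ß = 0.80"); true difference zero. The SDs and correlations by visit used below are assumptions, because the documents give none.

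**1. The plan's own figure.** n per arm = 2 × (1.645 + 0.842)² / 0.4² = 2 × 6.185 / 0.16 = 77.3, rounded up to 78, or 156 in total. With 78 per arm the SE is √(2/78) = 0.160 SD and power is Φ(0.4/0.1601 − 1.645) = Φ(0.853) = 0.803. The stated size is reproduced, and nothing below changes it.

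**2. Model SE against true SE.** With complete data, equal arms and a saturated time by group part, the random-intercept model estimates the total variance as the mean of the three visit variances. For visit k:

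- model SE = √(2/n × mean of SD²)
- true SE = √(2/n × SD_k²)
- ratio R_k = √(mean of SD²) / SD_k
- true one-sided error of a nominal 5% limit = Φ(−1.645 × R_k)

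The SDs are those left after baseline adjustment. The error depends only on R_k, so dividing by the baseline SD (taken as fixed) does not alter it.

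**3. Results with complete data.** For 0.9:1:1.1 the mean square is (0.81 + 1 + 1.21)/3 = 1.0067, with root 1.0033. At T3, R = 1.0033/1.1 = 0.912, and Φ(−1.645 × 0.912) = Φ(−1.500) = 6.7%. The model SE is 0.161 at every visit, against true SEs of 0.144, 0.160 and 0.176.

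| SD ratio T1:T2:T3 | R at T1 / T2 / T3 | True error (%) at T1 / T2 / T3 |
|---|---|---|
| 1:1:1 | 1.000 / 1.000 / 1.000 | 5.0 / 5.0 / 5.0 |
| 0.95:1:1.05 | 1.054 / 1.001 / 0.953 | 4.2 / 5.0 / 5.8 |
| 0.9:1:1.1 | 1.115 / 1.003 / 0.912 | 3.3 / 4.9 / 6.7 |
| 0.8:1:1.2 | 1.267 / 1.013 / 0.844 | 1.9 / 4.8 / 8.2 |

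If the variance fell over follow-up, the pattern would reverse.

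**4. Equal raw SDs do not settle it.** Suppose raw SDs are equal and baseline correlations fade as 0.60, 0.50, 0.35. The common slope is b = 0.483. The residual variance 1 − 2bρ + b² is then 0.654, 0.750 and 0.895 (SDs 0.81, 0.87, 0.95), with mean 0.766. At T3, R = √(0.766/0.895) = 0.925 and the error is 6.4%. A simulation of 6,000 trials gave 5.9%, with Monte Carlo error of about 0.3 points. Milder fading (0.50, 0.45, 0.40) gives 5.5%.

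**5. Unequal correlation alone.** Take equal SDs and correlations of 0.65 (T1-T2), 0.65 (T2-T3) and 0.42 (T1-T3). With complete data the error is 5.0% at every visit. With about 30% monotone dropout (per arm: 55 complete, 11 missing T3, 12 missing T2 and T3) it is 5.0, 4.9 and 5.3%, a shift of about 0.3 points at T3.

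**The case against.** The strongest reply is that the article never says the participant effect is the only covariance term. It names SPSS 20, whose mixed models accept a residual structure alongside a random participant effect, and a condensed article may leave that structure to the analysis plan. This stands in part: a heterogeneous-variance residual could accompany the random effect. But the article does choose to state the random part. An unstructured residual cannot be added to it, because three visits supply six variances and covariances and the unstructured matrix uses all six, leaving none to identify the intercept variance. The text therefore points to a restrictive model and does not merely leave the detail open.

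Second, a reader might infer that the intervals are in fact too narrow at one visit and too wide at another. The documents do not support that: they give no SD or correlation by visit, and with equal adjusted SDs the error is exactly 5.0%.

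Third, a reader might infer that the plan holds each visit's interval against -0.4. It does not say so. Sample size names no visit, and Clinical evaluation presents the visit-specific effect sizes as a measure of magnitude, without an interval. The concern therefore applies to whichever visit is used.

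Fourth, unequal visit spacing might suggest that the equal-correlation assumption does the damage. Step 5 shows that it hardly matters. Nor can a power loss at T1 be quantified, since the margin is on the baseline SD scale and the documents do not relate that SD to the SD at T1.

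**Conclusion.** The point holds in conditional form. On its plain reading, the stated model assumes one residual variance across 3, 6 and 12 months, and the interval for any single visit inherits that assumption. If the baseline-adjusted variance rises over follow-up, the one-sided error at 12 months exceeds 5%: to about 5.8% for a mild rise (0.95:1:1.05), 6.7% for a moderate one (0.9:1:1.1) and 8.2% for a marked one (0.8:1:1.2). The 3-month interval then becomes conservative. These figures rest on assumed SD ratios, complete data, equal arms and normal quantiles. If the variances are equal there is no error. Severity is minor: the sample size is untouched and no inflation is demonstrated, but the remedy is valid whether or not the variances differ.

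**What to change.** Replace the participant random intercept by an unstructured within-participant covariance over T1 to T3, fitted by REML with small-sample degrees of freedom. Name a heterogeneous-variance structure as the fallback if the fit does not converge. Take from this model the arm difference and its interval at whichever visit is used for the -0.4 test, and name that visit. A baseline by time interaction is optional; it lets the baseline slope differ between visits.

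The cost is a sentence or two in the analysis plan, with no new data. The covariance goes from two parameters to six, and the optional interaction adds two slopes, which is modest for 156 participants. The downside is a small risk of non-convergence, which the fallback covers.

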### Randomisation and blinding

Randomisation will take place at an individual level stratified by mental healthcare centre. The allocation will be conducted centrally at the VU Amsterdam by an independent team of researchers which is not involved in the trial. A computerised random number generator [39] is used to produce the allocation scheme with an allocation ratio 1:1. Subjects will be randomised into two groups: bCBT or TAU. The allocation is concealed, researchers and clinicians will be unknown to the randomisation scheme. Blinding for the treatment is not possible as it will be clear to both therapists and patients when the treatment is blended or not. However, the assessor conducting the M.I.N.I. at follow-up will be blinded to treatment status. The flowchart of the study is presented in Fig. 1, according to CONSORT guidelines [40].

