#### Economic evaluation

We will perform an economic evaluation from societal perspective, conducting a cost-effectiveness analysis (CEA) and cost-utility analysis (CUA). The CEA will be based on treatment response, defined as a 50 % pre-post reduction of QIDS-SR depressive symptoms [49]. The CUA will be conducted using quality adjusted life years (QALYs) as a generic measure of health gains. Multiple imputation using chained equations (MICE) will be used to impute missing cost and effect data. Predictive Mean Matching will be used to account for the skewed distribution of costs [70]. Variables that will be included in the multiple imputation model are variables related to missingness, variables related to costs and effects at 12 months of follow-up and all variables included in the analysis model. The number of imputations will be increased until the fraction of missing information (FMI) is 5 % or less [70]. The completed datasets will be analysed separately and pooled using Rubin’s rules [71].

Multilevel analyses with adjustment for mental health care institution will be done to estimate differences in costs and effects between bCBT and TAU while correcting for potential effect modifiers and confounders. Incremental cost-effectiveness ratios (ICERs) will be calculated by dividing the difference in costs by the difference in effects. Bias-corrected and accelerated bootstrapping with 5000 replications will be used to estimate statistical uncertainty. Bootstrapped cost-effect pairs will be plotted on cost-effectiveness planes (CE planes) to visualize the uncertainty surrounding the ICERs. Moreover, for decision-making purposes cost-effectiveness acceptability curves will be estimated showing the probability that bCBT is cost-effective in comparison with TAU at a range of different ceiling ratios. Finally, to test the robustness of our findings, sensitivity analyses will be performed. First, the economic evaluation will be conducted from a healthcare perspective. Secondly, a per protocol analysis will be done in which only participants completing the bCBT treatment protocol will be included.

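### The clinical non-inferiority model omits centre, the stratification factor; if centre is prognostic and the arms are balanced within centres, the interval is slightly too wide

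*Protocol article*

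**What the plan says.** Three places in the protocol article bear on this.

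- *Randomisation and blinding*: "Randomisation will take place at an individual level stratified by mental healthcare centre". Allocation is 1:1 from a computerised generator. Blocking within centres is not mentioned.
- *Clinical evaluation*: continuous outcomes at 3, 6 and 12 months go into a mixed model with a participant random effect and time, group and "time x group as fixed effects, with baseline scores as a single covariate". Effect sizes are the model's group estimates divided by the pooled baseline standard deviation.
- *Economic evaluation* (planned analyses): "Multilevel analyses with adjustment for mental health care institution will be done", and this covers differences in both costs and effects.

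The *Sample size* section sets the criterion. With 78 patients per arm, the lower limit of a one-sided 95 % interval "will be above a non-inferiority limit of -0.4" with 80 % power, "if we assume that there is no difference between the standard and blended depression treatment".

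**The concern.** Stratifying by centre makes the arms alike in their mix of centres. The estimated difference then varies less from trial to trial than it would without stratification. A model without centre does not see that gain: it leaves between-centre variation in the residual and reports a standard error for a noisier design. In a non-inferiority trial this pulls the lower limit towards the margin, so a treatment that is truly no worse passes less often than it could.

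The omission reads as a choice, not as a detail left for later. The article lists the clinical model term by term and calls baseline the single covariate, yet for the same patients it treats institution as worth adjusting for in the economic analysis. It gives no reason for the difference. The Dutch target of 156 also carries no stated allowance for drop-out, unlike the European target, which is raised from 1052 to 1200. Precision that costs nothing is therefore worth keeping.

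**Working it through.** **Inputs from the article.** 78 per arm; margin 0.4 in standard deviation units; true difference 0; one-sided error 0.05; power 0.80; allocation 1:1; stratification by centre.

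**Assumptions.** The outcome standard deviation is 1 on the scale of the margin. ρ is the between-centre share of the baseline-adjusted outcome variance. The article gives neither ρ nor the number of centres, so ρ is taken as 0.01, 0.05 and 0.10.

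**Step 1: reproduce the plan's figure.** n per arm = 2 × (1.645 + 0.842)² / 0.4² = 77.3, rounded up to 78, or 156 in total. This matches. The standard error is √(2/78) = 0.1601, the half-width of the 90 % interval is 1.645 × 0.1601 = 0.2634, and power is Φ(0.4/0.1601 − 1.645) = 0.803.

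**Step 2: leave centre out when allocation is balanced within centres.** The model still reports SE_m = √(2/78) = 0.1601. The true standard error is SE_t = √(2(1 − ρ)/78).

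- Ratio: SE_m/SE_t = 1/√(1 − ρ)
- True one-sided error: 1 − Φ(1.645/√(1 − ρ))
- Power without centre: Φ((0.4 − 0.2634)/SE_t)
- Power with centre: Φ(0.4/SE_t − 1.645)

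For ρ = 0.05, SE_t = 0.1561. The error is 1 − Φ(1.688) = 0.0457. Power is Φ(0.875) = 0.809 without centre and Φ(0.918) = 0.821 with it.

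| ρ | SE too large by | Half-width without / with centre | One-sided error without centre | Power without / with centre |
|---|---|---|---|---|
| 0.01 | 0.5 % | 0.263 / 0.262 | 4.9 % | 80.4 / 80.7 % |
| 0.05 | 2.6 % | 0.263 / 0.257 | 4.6 % | 80.9 / 82.1 % |
| 0.10 | 5.4 % | 0.263 / 0.250 | 4.1 % | 81.6 / 83.8 % |

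In patients: without centre, the narrower interval would need 156/0.95 = 164 at ρ = 0.05 or 156/0.90 = 173 at ρ = 0.10, that is 8 or 17 more.

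**Step 3: check by simulation.** This used one time point, baseline adjustment, 156 patients, 5 or 10 centres of nearly equal size and 4000 runs per setting (Monte Carlo error about 0.003 on an error rate). It approximates the planned repeated-measures model.

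- Blocks within centre, ρ = 0.10: one-sided error without centre 0.044; mean width of the 90 % interval 0.525–0.528 without centre and 0.503–0.504 with it.
- Blocks within centre, ρ = 0.05: error without centre 0.050 (5 centres) and 0.039 (10 centres), scattered around the predicted 0.046; width 0.528–0.531 without centre and 0.517–0.519 with it.
- No blocks, or ρ = 0: error without centre 0.044–0.054, so the interval is about correctly sized.
- Least favourable case for adding centre (no blocks, ρ = 0, 10 fixed centre terms): width rises from 0.533 to 0.550 and power falls from 0.789 to 0.767.

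**The case against.** The strongest reply is that little is at stake. The interval is too wide only if centre still predicts outcome after baseline adjustment and the arms are balanced within centres. The article quantifies neither and does not mention blocks. Where both hold, the error is on the safe side, and power without centre (80.4–81.6 %) still meets the planned 80 %. This stands, and it limits the point to a cheap improvement.

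It can also be said that the two analyses do not strictly contradict each other. The economic effects are treatment response on the QIDS-SR and QALYs, and that model also corrects for effect modifiers and confounders. Adding centre would not make the two models identical. This stands too. The economic text shows only that institution was thought relevant.

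Finally, the word single may mean only that baseline enters as one covariate and not as a level of time. Even so, no centre term is listed, fixed or random.

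A reader might go further and infer that the analysis makes false non-inferiority more likely, for example because patients of one therapist resemble each other and therapist is not modelled either. The documents do not support that. They give no intraclass correlation and no number of patients per therapist, and they do not say whether therapists treat in one arm or both. If therapists treat in both arms, omitting therapist is conservative, as with centre. Usual care may consist of medication or running therapy, so equal clustering in both arms cannot be assumed. A therapist sensitivity analysis is also a detail that an article commonly leaves to the analysis plan.

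**Conclusion.** The point holds as a modest, conditional one. The factor used to stratify randomisation is left out of a clinical model that is otherwise fully listed. If centre is prognostic and allocation is balanced within centres, the interval judged against -0.4 is too wide by about 0.5 % to 5 % for centre shares of 1 % to 10 %, and 0.2 to 2.3 points of power are forgone. These shares are assumptions, and at 1 % the effect is negligible.

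It would be wrong to read this as an interval that is certainly mis-sized, as a threat to the type I error or as a fault in the sample size. The figure of 156 reproduces exactly and need not change. A treatment effect that itself varied between centres could alter the direction, but the article gives nothing from which to judge that.

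**What to change.** In *Clinical evaluation*, replace baseline as the single covariate with two covariates: baseline score and mental healthcare centre. Enter centre as fixed, or as random if there are many small centres. Apply the same model in the intention-to-treat and per-protocol analyses. Non-inferiority must be shown in both, and the per-protocol set is selected after randomisation, so balance within centres is no longer assured there.

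The cost is one model term and a few degrees of freedom. Centre is already recorded for the randomisation, so no new data are needed. With many fixed centre terms, no blocking and no centre effect, the change would itself cost about two points of power (0.789 to 0.767 in the simulation with 10 centres). That is the reason to choose between fixed and random by the number and size of centres, and to settle it before outcomes are compared by arm.

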### Planned statistical analyses

In a non-inferiority trial, the study objective should be achieved in both the intention to treat and per-protocol population [68]. Analysis will be based on intention to treat (ITT) design, including all participants randomised in the study. Participants will be encouraged to provide assessment data, regardless of treatment adherence. Additionally, per-protocol (PP) analysis will be conducted, including only participants who followed the treatment protocol of the assigned treatment. Non-inferiority should be demonstrated also in the PP analysis, because ITT tends to dilute differences [69]. All analyses will be performed using the Statistical Package for the Social Sciences (SPSS), version 20.0.

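### Response and remission are compared with unadjusted tests that ignore centre and baseline severity and have no stated link to the imputed, centre-adjusted response analysis in the same article

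*Protocol article*

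**What the plan says.** Under Planned statistical analyses, Clinical evaluation, the protocol article fixes the method for the binary outcomes: "Differences in response and remission rates, as well as adherence rates will be examined using" t-tests and χ²-tests. It names no covariate, no centre term and no handling of missing responses for these rates. It also names no instrument or time point for response or remission. Continuous outcomes at T1 to T3 get a mixed model with the baseline score as covariate.

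Three other places bear on this:

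- **Population.** The opening of Planned statistical analyses says "Analysis will be based on intention to treat (ITT) design, including all participants randomised in the study". It adds that "Participants will be encouraged to provide assessment data, regardless of treatment adherence".
- **Economic evaluation (under Planned statistical analyses).** "The CEA will be based on treatment response, defined as a 50 % pre-post reduction of QIDS-SR depressive symptoms". "Multiple imputation using chained equations (MICE) will be used to impute missing cost and effect data", with pooling by Rubin's rules. "Multilevel analyses with adjustment for mental health care institution will be done to estimate differences in costs and effects between bCBT and TAU".
- **Randomisation and blinding.** "Randomisation will take place at an individual level stratified by mental healthcare centre", and the number generator is used to "produce the allocation scheme with an allocation ratio 1:1".

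**The concern.** A t-test or χ²-test is a positively stated choice, not a detail left for later. It leaves out the stratification factor and a baseline measure that every randomised patient will have, because baseline is completed before randomisation. If centre or baseline severity predicts outcome, the comparison gives up precision in a trial of 78 per arm.

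The second issue is the population. The mixed model lets patients with partial follow-up contribute to the continuous outcomes, and imputation does so for the economic outcomes. Nothing stated does this for clinical response and remission, so the route from the declared population to these comparisons is open. Follow-up is by online self-report through an e-mailed link, so some missing responses are foreseeable.

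The third is consistency. The effect difference in the cost-effectiveness ratio is built on QIDS-SR response, imputed and adjusted for institution. A clinical response difference from an unadjusted test could disagree with it, and the article does not say which is the trial's response result.

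**Working it through.** **1. The stated sample size reproduces.** Inputs from Sample size: margin 0.4 SD, true difference 0, one-sided 5 %, power 0.80.

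n per arm = 2(1.645 + 0.842)² / 0.4² ≈ 77.3, rounded up to 78; total 156, as stated. The European figure also reproduces: 2(1.960 + 1.282)² / 0.2² ≈ 525.4, rounded up to 526; total 1052. No stated figure is wrong, and both calculations concern the continuous symptom outcome, not response or remission.

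**2. The two planned analyses side by side.**

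| | Clinical evaluation | Economic evaluation |
|---|---|---|
| Response definition | not given | 50 % reduction on QIDS-SR |
| Time point | not given | imputation model refers to effects at 12 months |
| Missing data | not stated for rates | multiple imputation, Rubin's rules |
| Centre | no term | multilevel, adjusted for institution |
| Other adjustment | none | potential effect modifiers and confounders |
| Method | t-tests, χ²-tests | multilevel model |

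The two differ in adjustment, and only one states how missing outcomes are handled. Whether they estimate the same quantity depends on a definition and time point that the clinical section does not give.

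**3. Precision of an unadjusted response difference.** Assumption: 50 % response in both arms and equal loss per arm; the article gives neither rate. The 95 % half-width is 1.96·√(2·0.25/m), where m is the number analysed per arm.

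| Missing per arm | m | Half-width (points) |
|---|---|---|
| 0 % | 78 | 15.7 |
| 10 % | 70.2 | 16.5 |
| 20 % | 62.4 | 17.5 |
| 30 % | 54.6 | 18.8 |
| 40 % | 46.8 | 20.3 |

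An interval displays this width; a p-value does not.

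**4. Possible shift if only observed cases were tested.** This is a conditional illustration, since the article does not say so. Assume true response of 50 % in both arms, a fraction d missing, and response r among the missing. The observed rate is (0.5 − d·r)/(1 − d).

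| Missing bCBT / TAU | r | Observed bCBT | Observed TAU | Spurious difference (points) |
|---|---|---|---|---|
| 20 % / 20 % | 30 % | 0.550 | 0.550 | 0 |
| 30 % / 20 % | 50 % | 0.500 | 0.500 | 0 |
| 30 % / 20 % | 30 % | 0.586 | 0.550 | +3.6 |
| 30 % / 20 % | 10 % | 0.671 | 0.600 | +7.1 |
| 40 % / 20 % | 30 % | 0.633 | 0.550 | +8.3 |
| 40 % / 20 % | 10 % | 0.767 | 0.600 | +16.7 |

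With these values of r, the shift favours the arm that loses more patients. With 20 % missing in bCBT and 30 % in TAU it becomes −3.6 (r = 30 %) or −7.1 (r = 10 %). It is zero when missingness is equal across arms, as in the first row, or unrelated to response, as in the second.

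**The case against.** Three stronger readings are tempting, and the document supports none of them.

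- **That the tests use observed cases only, and so contradict intention to treat.** The clinical section is silent on missing responses. A χ²-test can be run on imputed data or with missing counted as non-response, and the general statement on population applies to the planned analyses as a whole. A condensed article may leave this handling to the full protocol or analysis plan. The link is unstated; it is not broken.
- **That a non-significant test would be read as equivalence.** The non-inferiority limit is a standardised difference on depressive symptoms, judged by a confidence limit. Response and remission are not listed among the primary or secondary outcome measures, and nothing says that a null χ²-test will support non-inferiority.
- **That the plan certainly yields two response differences for one quantity.** Without an instrument or time point for clinical response, the two may not be the same endpoint.

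It is also fair to say that an unadjusted comparison of proportions is valid under 1:1 randomisation, that the plan seeks assessments regardless of adherence, and that imputation would not remove bias from dropout which the observed variables do not explain.

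What this leaves standing is the choice of method. The article commits to tests that omit the stratification factor and baseline severity, while planning elsewhere the imputation and institution adjustment that would serve these outcomes better.

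**Conclusion.** The point holds as a better-method point on supportive outcomes. The stated tests for response and remission leave out centre and baseline severity, and no stated method carries randomised patients without follow-up into them. If definition and time point match those of the economic evaluation, two response differences would appear in one trial. The primary PHQ-9 analysis is untouched.

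No size can be fixed from the document. The half-widths of 15.7 to 20.3 points rest on an assumed 50 % response and 0 to 40 % loss. The shift of 0 to about 17 points rests on assumed dropout that is both unequal and informative, and on the further supposition that only observed cases are tested. Imputation would reduce such a shift only as far as observed variables explain the dropout.

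**What to change.** In Clinical evaluation, replace the t-tests and χ²-tests for response and remission with a logistic model, or a multilevel logistic model, that includes treatment, baseline severity and centre. Fit it to the multiply imputed data already planned for the economic evaluation and pool with Rubin's rules. Report risk differences with confidence intervals.

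State the instrument, threshold and time point for clinical response and remission. Where the response definition and time point match those of the economic evaluation, use the same estimate in the cost-effectiveness analysis; where they do not, say that the two are different endpoints.

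The cost is a change of analysis wording and slightly more analysis work. If the clinical rates use PHQ-9 or earlier time points, those scores must be among the variables imputed. No data collection changes, and the article reports recruitment as ongoing, so the wording can be settled before analysis.
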